### 8.3 Post-vaccination Reactions

The procedure for evaluation of post-vaccination reactions including immediate reactogenicity, solicited AEs (local and systemic reactogenicity recorded till 14 days after vaccination) and unsolicited AEs till 28 days after vaccination as described in details in Section 7.

*Information contained in this publication is the property of EVI and ICGEB and is confidential and will not be disclosed to third parties without written authorization from EVI and ICGEB. No part of this document may be reproduced, stored in a retrieval system or transmitted in any form or by any means -electronic, mechanical, recording or otherwise - without the prior authorization of EVI and ICGEB*

[figure not shown][figure not shown]

## 8.4 Adverse Events

### 8.4.1 Definition of an Adverse Event

Adverse Event (AE) is defined as any untoward medical occurrence in a subject or clinical investigation subject administered a pharmaceutical product and which does not necessarily have a causal relationship with this treatment. An AE can therefore be any unfavourable and unintended sign (including an abnormal laboratory finding), symptom, or disease temporally associated with the use of the Medicinal (investigational) product (ICH GCP definition).

### 8.4.2 Reporting of Adverse Events

To ensure subject safety, every AE, regardless of suspected causality, occurring after the subject has received the first dose of the vaccine till 28 days after the subject has received each dose of the vaccine will be reported. Information about all adverse events, whether volunteered by the subject, discovered by investigator questioning, or detected through physical examination, laboratory test or other means, will be collected and recorded on the Adverse Event Case Report Form and followed as appropriate. Thus, AEs will be collected through both solicited and unsolicited means and subsequently coded in tabular form using the latest version of MedDRA Adverse Event Dictionary. The subjects will be encouraged to report signs, symptoms, and any changes in health to the Investigator. Severity of each AE will be determined by the staff based on observation and questioning of the subjects. The Investigator will judge the relationship of the event to the study treatments.

Adverse events occurring before the subject has signed the informed consent as well as those which occur in the screening period are recorded on the Medical History. Abnormal laboratory values or test results constitute adverse events if they are not a part of any specific diagnosis, induce clinical signs or symptoms, require any action to be taken or any intervention to be made, and are considered as clinically significant. Such clinically significant abnormal lab values will be recorded on the Adverse Events Case Report Form under the signs, symptoms or diagnosis associated with them and will be followed till resolution or stabilization of the same.

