## 8 SAFETY MONITORING

### 8.1 Introduction

The collection, recording, assessment and reporting of adverse events (AE) and serious adverse events (SAE) represent the core activities for the safety evaluation. These activities are under the direct responsibility of the Investigator.

The recording of adverse events is an important aspect of study documentation as the evaluation of the safety of three (3) intramuscular injections of the investigational vaccine (JAIVAC-1 – Montanide ISA 720 malaria vaccine) in comparison with that of the control vaccine (Hepatitis B vaccine) is the primary objective of this study. The procedure for evaluation of immediate reactogenicity, solicited adverse events and unsolicited adverse events is described Section 7. The investigator is responsible for the detection and documentation of events meeting the definition of an adverse event (AE) or a serious adverse event (SAE) as provided in Sections 8.4 and 8.5 of this protocol. This includes the evaluation of its seriousness, its severity, and the causal relationship to the investigational vaccine and/or concomitant therapy.

At each visit, the investigator will assess whether any AE including laboratory abnormalities has occurred. The investigator shall inquire for unsolicited AEs with non-suggestive questions to the subject at each study visit. The investigator shall attempt to establish a diagnosis of the event based on signs, symptoms and/or other clinical information. The diagnosis shall be recorded as the AE and/or SAE and not the individual symptoms.

If a laboratory abnormality or other abnormal assessment meets the definition of an AE or SAE, the Adverse Event or Serious Adverse Event Form shall be completed as appropriate. A diagnosis, if known or clinical signs and symptoms if diagnosis is unknown, rather than the laboratory abnormality shall be reported. If no diagnosis is known and clinical signs and symptoms are not present, then the abnormal finding shall be recorded. The subject shall be observed and monitored carefully until the AE resolves, the condition stabilises or its cause is identified completely. The investigator is responsible for ensuring that follow-up includes any supplemental investigations that may be indicated to elucidate the nature and/or the cause of the event.

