#### **8.4.4 Assessment of Severity of Adverse Events**

The following three-point rating scale will be used for rating the severity of all unsolicited AEs/SAEs (apart from the ones covered in Section 7.2):

Grade 1: Awareness of signs or symptoms, no interference with daily activities

Grade 2: Symptoms cause discomfort with some interference with daily activities

Grade 3: Disabling, the subject is unable to conduct a range of daily activities

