#### 11.5.1.3 Analysis of Overall Safety

The safety analysis will include all randomised subjects who have received at least one dose of either of the assigned study vaccines. The overall percentage of subjects with at least one reported adverse event / serious adverse event, with date of onset up to 28 days after vaccination will be tabulated with 95% confidence intervals, by type of adverse event; by severity; and by causality. These events will be summarised and classified by System Organ Class and preferred term MedDRA. They will be displayed by vaccine group as both frequencies and percentages on the ITT data set. All reported adverse events that start post-vaccination would be tabulated. If a given disease is already reported as ongoing at the first visit on the medical history pages, it will be counted and tabulated as a vaccine emergent adverse event only if it worsens after the vaccination with the study vaccines. For each vaccine group vital sign parameters will be summarised visit wise as number of subjects, mean, SEM, median minimum, maximum and range. The changes in vital

*Information contained in this publication is the property of EVI and ICGEB and is confidential and will not be disclosed to third parties without written authorization from EVI and ICGEB. No part of this document may be reproduced, stored in a retrieval system or transmitted in any form or by any means -electronic, mechanical, recording or otherwise - without the prior authorization of EVI and ICGEB*

[figure not shown][figure not shown]

signs for every 30 minutes till 3 hours post-vaccination from pre-vaccination will be calculated and tabulated for each vaccine group.

The investigator will check the biological parameters (haematology and serum chemistry). Newly occurring or worsening lab abnormalities will be assessed and reported by the investigator as adverse events as applicable. Clinical laboratory results will be tabulated by vaccine group at each time point as both quantitative parameters (raw values) and qualitative parameters (relative positions regarding normal ranges in use in the laboratory). Serious adverse events and discontinuation due to adverse event(s) will be described in detail by vaccine group.

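### Section 8.4.2, read as written, denies adverse event status to symptom-free laboratory abnormalities, in conflict with sections 8.4.1 and 8.1; the AE incidence is affected, the laboratory tabulations are not

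*Supplement*

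**What the plan says.** Section 8.4.2 (Reporting of Adverse Events) sets the test for laboratory results: "Abnormal laboratory values or test results constitute adverse events if they are not a part of any specific diagnosis, induce clinical signs or symptoms". The same sentence continues: "require any action to be taken or any intervention to be made, and are considered as clinically significant". The next sentence says where such values go: they are "recorded on the Adverse Events Case Report Form under the signs, symptoms or diagnosis associated with them".

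Three other sections bear on the same question.

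- Section 8.4.1 defines an AE as possibly being "any unfavourable and unintended sign (including an abnormal laboratory finding), symptom, or disease" that is temporally associated with the product. It attaches no symptom or action condition.
- Section 8.1 has a paragraph that opens: "If a laboratory abnormality or other abnormal assessment meets the definition of an AE or SAE". It asks for the diagnosis if known and otherwise for the signs and symptoms. It ends: "If no diagnosis is known and clinical signs and symptoms are not present, then the abnormal finding shall be recorded".
- Section 11.5.1.3 (Analysis of Overall Safety) says: "Newly occurring or worsening lab abnormalities will be assessed and reported by the investigator as adverse events as applicable".

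Unsolicited AEs up to 28 days after each vaccination are a primary endpoint (4.6.1). Section 11.5.1.3 reports them as the percentage of subjects with at least one AE or serious AE, with 95% confidence intervals, by type, severity and causality. Biological safety, meaning haematology and chemistry against baseline, is a separate primary endpoint in 4.6.1. Section 11.5.1.3 tabulates those results by group and time point, as raw values and against the normal ranges.

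**The concern.** Take a healthy volunteer with a marked new ALT rise or neutrophil fall and no symptoms. Under 8.4.2 this is not an AE, because the symptom condition fails. Under 8.4.1 it can be one, and 8.1 tells the investigator how to name it. The protocol therefore gives two answers to whether the event exists in the AE data.

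The AE incidence is a primary safety result of a first-in-human study, and the arms are small enough for one subject to move it visibly. Causality assessment (8.4.5) and the AE follow-up rules (8.4.7) attach to AEs. An abnormality that is not classed as an AE has no recorded relatedness judgement, MedDRA term or place in the severity breakdown.

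**Working it through.** The protocol makes no sample size calculation and gives no figure on this point, so there is none to reproduce. The check compares the rules and then works out the effect per subject.

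**1. The rules side by side.** Write D for not part of a diagnosis, S for induces signs or symptoms, A for requires action, and C for clinically significant.

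- 8.4.2: AE if D and S and A and C. If S is false, the condition fails whatever A and C are. The section gives no other criterion for laboratory values. It then files them under an associated sign, symptom or diagnosis, which an isolated value does not have.
- 8.4.1: an abnormal laboratory finding can be an AE. S and A do not appear.
- 8.1: once the AE definition is met, record the diagnosis; failing that, the signs and symptoms; failing both, the abnormal finding. For a laboratory abnormality, the last step could never be reached if S were necessary. So 8.1 presupposes that S is not necessary.
- 11.5.1.3: its closing qualifier leaves open which rule governs.

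Sections 8.4.1 and 8.1 agree with each other; 8.4.2 agrees with neither.

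**2. Which samples are affected.** Doses are on Days 0, 28 and 180. Post-dose laboratory samples are on Days 28, 56, 180, 208 and 365, and the Day 28 and Day 180 samples are taken before vaccination (footnotes to Tables 1 and 7). Days since the last dose given:

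- Day 28: 28 − 0 = 28
- Day 56: 56 − 28 = 28
- Day 180: 180 − 28 = 152
- Day 208: 208 − 180 = 28
- Day 365: 365 − 180 = 185

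On nominal days, three of the five samples fall within the 28-day AE window. Appendix B lists 24 haematology and chemistry analytes (13 + 11).

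**3. Shift per subject.** The measure is the percentage with at least one AE, so reclassifying a laboratory event matters only for a subject with no other AE in the window. Shift = 1/n:

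- test arm: 1/10 = 10 points
- control arm of one cohort: 1/5 = 20 points
- controls pooled over cohorts: 1/15 = 6.7 points

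**4. Illustration for one test arm of 10.** Assume x subjects have a symptom-free, clinically significant abnormality and no other AE. The other subjects have no AE. The exact (Clopper-Pearson) 95% limits are the 0.025 quantile of Beta(x, n − x + 1) and the 0.975 quantile of Beta(x + 1, n − x).

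| x (assumed) | Counted, as 8.1 and 8.4.1 allow | Under 8.4.2 |
|---|---|---|
| 1 | 1/10 = 10% (0.3 to 44.5%) | 0/10 = 0% (0 to 30.8%) |
| 2 | 2/10 = 20% (2.5 to 55.6%) | 0/10 = 0% (0 to 30.8%) |
| 3 | 3/10 = 30% (6.7 to 65.2%) | 0/10 = 0% (0 to 30.8%) |

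The counts are assumptions; the protocol gives no expected rate of such abnormalities.

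**The case against.** The strongest reply is that nothing is lost from the primary safety data. Every scheduled laboratory value is kept in the biological safety endpoint and tabulated by group and visit. Values significantly outside the normal range are notified to the sponsor's medical monitor (7.2.7), and a laboratory abnormality is itself a listed ground for discontinuation (5.4.4). This stands. A reader might infer that symptom-free abnormalities vanish from the safety results, and the documents do not support that. The tabulations do not, however, supply relatedness, MedDRA coding or AE follow-up.

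Second, the clash can be put too strongly. Section 8.1 does not order every isolated abnormality to be recorded as an AE; its paragraph applies once the AE definition is met. Section 11.5.1.3 sets no rival rule. Section 8.4.2 says *if*, not *only if*. All of this stands, but 8.4.2 offers no other criterion, and 8.1 still presupposes what 8.4.2 excludes.

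Third, the drafters may have meant *or*. Section 8.4.2 itself speaks of AEs found by laboratory test, and its following sentence refers back to the values simply as clinically significant. That is plausible, but sites must apply the text they have. The CRF completion guidelines and the SAP are not shown and may carry a working rule. An SAP could flag laboratory values later, but it could not supply a causality judgement that was never made.

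Fourth, because investigators know the allocation (4.5), a reader might infer that the AE counts will be distorted between arms. Unblinded choice between two rules makes that possible, but nothing in the documents shows that it would happen, and the analysis is descriptive.

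**Conclusion.** The point holds as a contradiction between stated rules, and the sponsor should correct it. As written, 8.4.2 excludes symptom-free laboratory abnormalities from AE status, against 8.4.1 and the recording rule in 8.1. The effect is limited to the AE incidence, its severity and causality breakdown, and AE follow-up, for abnormalities seen within 28 days of a dose. It does not extend to the Day 180 and Day 365 samples, which lie outside the AE window under either reading, or to the laboratory tabulations.

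The size is 10 points per affected subject in a test arm of 10, and 20 points in a control arm of 5 or 6.7 points among 15 pooled controls. These figures assume that the subject has no other AE in the window. The choice between the two control figures depends on whether controls are reported by cohort or pooled, because section 11.5.1.3 says only that results are given by vaccine group.

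**What to change.** Reword the 8.4.2 sentence to agree with 8.4.1 and 8.1: an abnormal value not explained by a recorded diagnosis is an AE if the investigator judges it clinically significant, or it induces signs or symptoms, or it requires action. Add that an isolated abnormality is recorded under its own name, and bring the CRF completion guideline into line.

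The grading text needs a matching addition. The unsolicited scales in 7.2.5 and 8.4.4 presuppose symptoms; the lowest level in 8.4.4 is "Grade 1: Awareness of signs or symptoms, no interference with daily activities". The protocol should state how a symptom-free laboratory event is entered on these scales, or the severity breakdown will have no category for it.

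The cost is one reworded sentence, a short addition to the grading text, a change to the guideline, and a slightly higher AE count.

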### 8.4.3 Documentation of Adverse Events

Whenever possible, AEs should be documented in terms of a diagnosis or syndrome rather than multiple symptoms that are clearly manifestations of the same diagnosis/syndrome. If a diagnosis can not be obtained then enter each sign or symptoms as separate events. Pre-existing conditions or signs and/or symptoms (including any which are not recognised at study entry but are recognised during the study period) present in a subject prior to Visit 2 should be recorded in the Medical History form in the subject's CRF.

AEs that occur after subject is enrolled in the study, but prior to first vaccination, will be documented in the medical history and pre-existing conditions sections of the CRF. Hospitalisation for either elective surgery related to a pre-existing condition which did not increase in severity or frequency following initiation of the study, or for routine clinical procedures (including hospitalisation for "social" reasons) that are not the result of an AE, must be recorded on the Adverse Event page of the CRF. The relationship to vaccination will be checked "No". These AEs are not considered as SAEs.

*Information contained in this publication is the property of EVI and ICGEB and is confidential and will not be disclosed to third parties without written authorization from EVI and ICGEB. No part of this document may be reproduced, stored in a retrieval system or transmitted in any form or by any means -electronic, mechanical, recording or otherwise - without the prior authorization of EVI and ICGEB*

[figure not shown][figure not shown]

As far as possible, each adverse event will be described by:

1. Duration of AE (start and end dates)
2. Severity of AE (as per scoring/grading system)
3. Relationship to the study vaccine (related, unrelated)
4. Action(s) taken and, as relevant, the outcome.

#### **8.4.4 Assessment of Severity of Adverse Events**

The following three-point rating scale will be used for rating the severity of all unsolicited AEs/SAEs (apart from the ones covered in Section 7.2):

Grade 1: Awareness of signs or symptoms, no interference with daily activities

Grade 2: Symptoms cause discomfort with some interference with daily activities

Grade 3: Disabling, the subject is unable to conduct a range of daily activities

#### **8.4.5 Assessment of Causality of Adverse Events**

Assessment of causality Adverse Event (related or not related) will be done by the Investigator. The following scale will be used for rating the causal relationship of the AE to the investigational product (vaccine):

##### **Causality Assessment: Related**

The adverse event is clearly related to the vaccine i.e. an event that follows a reasonable temporal sequence from administration of the vaccine, follows a known or expected response pattern to the suspected vaccine, that is confirmed by improvement on stopping and reappearance of the event on repeated exposure and that could not be reasonably explained by the known characteristics of the subject's clinical state.

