## 4.6 Definition of Study Endpoints

### 4.6.1 Primary Endpoint(s)

The safety profile will be assessed on the basis of the following criteria

- Immediate reactogenicity (any event occurring within the first three (3) hours recorded every 30 minutes after each vaccination, with emphasis on allergic reactions)
- Local and systemic reactogenicity (solicited adverse events occurring from three (3) hours post-vaccination on Day 0 till Day 14 after each dose)
- Any unsolicited adverse events 28 days after each vaccination
- Any Serious Adverse Event (SAE) occurring from the first dose of vaccine till the last follow-up visit.
- Biological safety, 28 days after each vaccination, in reference with the baseline before the first dose, by measuring the following parameters:

- Haematology: RBC count, Haemoglobin\*, Haematocrit/Packed Cell Volume (PCV), MCV (Mean Corpuscular Volume), MCH (Mean Corpuscular Haemoglobin), MCHC (Mean Corpuscular Haemoglobin Concentration), Platelet Count and Total Leukocyte Count (TLC) along with Differential Leukocyte Count (DLC) on Days -14, 28, 56, 180, 208, 365.

\*If the haemoglobin drops below 13 gm/dL, then a direct Coomb's test and a peripheral blood smear/film will be prepared and examined for evidence of possible haemolysis.

- Serum Chemistry: Potassium, Sodium, AST, ALT, Direct, Indirect and Total Bilirubin, Alkaline Phosphatase, Gamma Glutamyl Transpeptidase ( $\gamma$ GT), Creatinine, and Random blood glucose on Days -14, 28, 56, 180, 208, 365.

The Investigator will be responsible for causality assessment i.e. assessment of the relationship of the AE to the assigned study vaccines, using the following definitions: related or not related.

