### 8.2 Data Safety Monitoring Board

An independent Data Safety Monitoring Board (DSMB) will be set up prior to initiating the study comprising of three (3) independent clinicians with relevant expertise in the field of vaccines development and evaluation of vaccine safety along with the designated Local Safety Monitor (who would be a designated personnel from the investigational site but independent of the study team). Dose escalation to the next higher dosage cohort of JAIVAC-1 – Montanide ISA 720 will occur after the safety data from the first dose of vaccine through Day 14 day for all 15 subjects of the previous dosage cohort has been reviewed by the DSMB.

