##### **Causality Assessment: Not Related**

The adverse event is clearly not related to the vaccine i.e. another cause of the event is most plausible; and/or a clinically plausible temporal sequence is inconsistent with the onset of the event and the vaccine administration; and/or a causal relationship is considered biologically implausible.

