### 8.5.3 Processing and Regulatory Submission of SAE Reports

All SAE reports will be processed, evaluated and reported to the Sponsor, IEC(s)/IRB(s) and regulatory agencies as per applicable timelines.

Every serious adverse event must be reported by the Investigator to the Medical and Safety Monitor, DLS and the Sponsor representatives (ICGEB/EVI) within 24 hours of the knowledge of SAE.

The Medical and Safety Monitor will send the following to the Sponsor's Contact Person; preferably by e-mail or fax:

- Reports for death or life-threatening SAEs not later than one (1) business day from Date of Receipt from the Investigator
- Reports for other SAEs not later than two (2) business days from the Date of Receipt from the Investigator
- Reports on pregnancy cases in female partner of male subjects (Pregnancy Reports), as applicable not later than two (2) business days from the Date of Receipt from the Investigator

*Information contained in this publication is the property of EVI and ICGEB and is confidential and will not be disclosed to third parties without written authorization from EVI and ICGEB. No part of this document may be reproduced, stored in a retrieval system or transmitted in any form or by any means -electronic, mechanical, recording or otherwise - without the prior authorization of EVI and ICGEB*

[figure not shown][figure not shown]

In addition, the following SAE Reporting timelines will be followed:

- The Principal Investigator will send the SAE report to the site EC within 7 working days from the day of awareness of occurrence of the SAE
- The ICGEB Representative will send the SAE report to the ICGEB IRB within 7 working days from the day of awareness of occurrence of the SAE
- DLS will send the SAE Reports for unexpected and related SAEs, which are deaths/life-threatening SAEs occurring at study site to the DCGI within 7 calendar days from the day of awareness of occurrence of the SAE with a follow-up report sent within the next 8 calendar days.
- DLS will send the SAE Reports for all other SAEs occurring at study site to the DCGI within 14 calendar days from the day of awareness of occurrence of the SAE

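### The causality rule in section 8.4.5 makes recurrence on re-exposure a condition of Related and needs positive grounds for Not Related, so many events fit neither of the two permitted classes

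*Supplement*

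**What the plan says.** The protocol uses a two-way causality classification. Section 8.4.5: "Assessment of causality Adverse Event (related or not related) will be done by the Investigator". The same pair appears under the primary endpoint in section 4.6.1, where the investigator makes an "assessment of the relationship of the AE to the assigned study vaccines, using the following definitions: related or not related". Section 8.4.3 has each adverse event described by one of the two, as far as possible, and section 8.5.4 applies the same criteria to serious events.

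The two definitions are built differently.

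- **Related** is cumulative. The event must be clearly related, with plausible timing and a pattern already known or anticipated for the vaccine, and must be one "that is confirmed by improvement on stopping and reappearance of the event on repeated exposure and that could not be reasonably explained" by what is known of the subject's clinical state.
- **Not Related** starts "The adverse event is clearly not related to the vaccine i.e. another cause of the event is most plausible" and adds, as alternatives, timing that does not fit or biological implausibility. At least one positive ground is needed.

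The classification is used in three places:

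- Section 11.5.1.3 tabulates the percentage of subjects with events, with 95% confidence intervals, "by type of adverse event; by severity; and by causality".
- Section 8.4.7 continues follow-up beyond the trial for all serious events, but for non-serious events only if they are related.
- Section 8.5.3 sets a 7-calendar-day report to the national regulator: "DLS will send the SAE Reports for unexpected and related SAEs, which are deaths/life-threatening SAEs occurring at study site". All other serious events go to the regulator within 14 calendar days.

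**The concern.** The confirmation clause describes a drug that is taken repeatedly, withdrawn and given again. Here each exposure is a single injection, so improvement on stopping has little meaning, and reappearance can be observed only after the next dose, if there is one. A well-timed reaction with no other explanation, seen once, fails Related for want of rechallenge. It also fails Not Related, because nothing positive speaks against the vaccine. The investigator must still choose.

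At stake are a breakdown of the safety data that the protocol lists under its primary endpoint, the extent of follow-up for some non-serious events, and the regulatory clock for the gravest ones. Investigators and assessors are unblinded (section 4.5). A rule that cannot be followed leaves the choice to individual judgement by people who know the allocation.

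**Working it through.** **1. The escalation calendar.** The protocol's own figure reproduces. Section 4.1 gives data to Day 14 plus a decision within 7 days: 14 + 7 = 21 days after the 15th subject's first dose, as stated.

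The review package in section 8.2 is "the safety data from the first dose of vaccine through Day 14 day for all 15 subjects of the previous dosage cohort". Enrolment of a cohort spans three days (section 4.1), the second dose is on Day 28, and the visit window is ±1 day (Tables 1 and 7). With the cohort's first subject at calendar day 0 and the 15th at day 2:

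- Day 14 of the 15th subject: 2 + 14 = 16.
- Decision due: 2 + 21 = 23, or 24 with the window.
- Earliest second dose in the cohort: 28 − 1 = 27, nominally 28.
- Gap between decision and first re-exposure: 27 − 24 = 3 to 28 − 23 = 5 days.

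At its own escalation review, 0 of 10 vaccinees can therefore have a Related event. A late decision would not change this for the required package, which stops at Day 14 after dose 1.

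**2. What a zero would hide.** The documents give no reaction rates, so the rates below are assumed. The probability of at least one reactor among 10 is 1 − (1 − p)^10.

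| Assumed true rate p | Expected reactors of 10 | P(at least one) | Related under the rule |
|---|---|---|---|
| 10% | 1 | 65% | 0/10 |
| 30% | 3 | 97% | 0/10 |
| 50% | 5 | 99.9% | 0/10 |

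The exact 95% interval for 0/10 runs from 0 to 1 − 0.025^(1/10) = 30.8%. It would be reported unchanged whatever the true rate.

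**3. The formal analyses.** Section 11.2 places these at 28 days after the third dose (180 + 28 = Day 208) and at the end of the study.

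- First seen after dose 1: two re-exposures are possible, at Days 28 and 180.
- First seen after dose 2: one is possible, 180 − 28 = 152 days later.
- First seen after dose 3: none, so the event can never be Related.
- Single occurrence, death, or withdrawal before re-exposure: never Related, whichever dose came before.

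**4. The second escalation on the fastest timeline.** Cohort 2 starts at day 23, and its 15th subject is dosed at day 25. The Day 14 data are complete at day 39, and the decision is due by day 46. Cohort 1 had its second dose on days 28 to 30, so it is then 46 − 30 = 16 to 46 − 28 = 18 days past it, and a Cohort 1 first-dose event could have recurred. Cohort 2's own earliest second dose is at day 23 + 27 = 50, so its reviewed events still cannot qualify.

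**5. The 7-day route.** It requires an event to be both unexpected and related. A fatal event cannot reappear, so no death can meet Related. A life-threatening event that the subject survives could in principle recur at a later dose, but rechallenge evidence would not normally exist within 7 days of its first occurrence. In addition, section 8.4.6 defines unexpected as inconsistent in nature or severity with the product information, while section 8.4.5 asks Related events to follow a known or anticipated pattern. The two conditions pull against each other.

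**The case against.** Several stronger readings are tempting, and the documents do not support them.

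- *The escalation decision rests on an empty causality analysis.* No causality table is planned for that review. Section 11.5.1.3 describes the study analyses, and no escalation criterion mentions causality. Immediate reactions, graded solicited events and unsolicited events are collected whatever their cause. Only the Related class is empty at that point; Not Related can still be filled.
- *No first-dose event can ever be Related.* One that recurs after dose 2 or 3 can qualify by Day 208, even if the recurrence then ends vaccination.
- *The error always runs in the reassuring direction.* Applied literally, the wording bars Related. But a plausible event fails Not Related too, and an investigator forced to choose could go either way.
- *Serious events go unreported.* Section 8.5.2 sends every one to the sponsor and the contract research organisation within 24 hours whatever its cause. Under section 8.5.3, deaths and life-threatening events are forwarded to the sponsor within one business day, the site ethics committee and the sponsor's review board are informed within 7 working days, and the regulator receives all other serious events within 14 calendar days. The loss is 14 − 7 = 7 days for one recipient.

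It is also fair to say that reactogenicity (section 11.5.1.2) and overall event percentages by vaccine group do not depend on causality, and that section 8.4.7 follows every event until it resolves or stabilises. All of this limits the damage. None of it repairs the definition, and no other section relaxes it. Trusting investigators' common sense means relying on them to ignore the written rule, each in their own way.

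**Conclusion.** The concern holds for the definition itself. Section 8.4.5 offers two classes that do not cover all events, and one carries a condition that many genuine vaccine reactions cannot meet. At each cohort's own escalation review the number of Related events is 0 of 10 by construction. At the interim and final analyses, an event can be Related only if it first occurred after dose 1 or 2 and came back. The breakdown by causality therefore cannot be filled correctly, the post-trial follow-up of related non-serious events inherits the fault, and the 7-day route for unexpected, related deaths is unreachable as written.

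This rests on a literal reading of the conjunctive wording and, for the calendar, on three-day enrolment and on-time decisions. It does not show that any escalation decision would change or that any serious event would escape reporting. Because the classification is made by the investigator under the protocol, a later analysis plan cannot mend it at the tabulation stage.

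**What to change.** Reconcile the definitions in section 8.4.5 so that every adverse event can be classified when it is assessed:

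- **Related:** a reasonable possibility that the vaccine caused the event, with plausible timing and no better explanation from another cause. Dechallenge, rechallenge and a known pattern count as supporting evidence, not as conditions.
- **Not Related:** every event that does not meet this, so that the two classes are exhaustive.

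Then check sections 8.4.7, 8.5.3, 8.5.4 and 11.5.1.3 against the new wording, in particular that an event can be both unexpected and related. Treating injection-site reactions as related by default is an optional convention and is not needed to close the gap.

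The cost is an amendment to the protocol and the case-report-form guideline, best made before first dosing. No extra data are collected. The reported count of related events may be higher.
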